**Results:**

We opened enrollment in September 2023. The initial results are expected to be published in late 2024. We predict that children in the CCT group will show a reduction in emotional symptoms; improvements in inhibition, shifting, and updating performance; and advances in math achievement from pre- to posttraining, and that these effects will be maintained at 1- and 3-month follow-ups, compared to children in the active control group.

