### Participants

A nonselect sample of children aged 8-10 years will be recruited from primary schools. An a priori power analysis revealed that 66 participants are required to detect small effects (*d*=0.20) approaching those reported by previous studies with 80% or greater power on primary outcome measures relative to controls [9,23,24]. To allow for approximately 30% attrition we will recruit 100 children proportionately balanced for sex and age across 8, 9, and 10 years. To incentivize enrollment and study completion, participating children will be compensated using monetary tokens redeemed at the end of the study; Aus $ 2.00 (US $1.31) for the completed questionnaires at each of 4 time points and Aus $ 2.00 (US $1.31) for each training session (~Aus $ 40.00; US $26.14 per participant). Given that teachers are required to supervise and monitor the daily training, they will be incentivized for their class’s participation (minimum 20 students) at the rate of 1 teacher relief day for each data collection time point (pre- and posttraining and 1- and 3-month follow-ups).

Primary and P-12 schools, as well as private, independent, and Catholic schools, will be approached regarding participation in the study. A recruitment package of materials (including a university ethics approval letter, gatekeeper permission request, pamphlet, study protocol, participant information sheets for parents, teachers and children, consent forms, and an information sheet about children’s anxiety and depression) will be sent to the school principal to determine interest in participation. Information sessions will be held face-to-face or using a video communications platform (eg, Zoom) for principals, teachers, and parents, as required.

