#### Training Groups

We will randomly assign participants to 1 of the 2 training groups. Groups comprise an experimental CCT group that will train using an adaptive Go/No-Go Task (aGo/No-Go) targeting inhibitory control, and an active control group that will train using a low-load task. The active control task does not require the same cognitive load as the aGO/No-Go task; thus, we do not expect it to produce emotional or cognitive changes. Children in both groups will undertake 10 minutes of training per day for 3 weeks, allowing 15 sessions to be completed.

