### Data Analytic Plan

Mixed between-within ANOVA will be used with Group (CCT, aGo/No-Go vs active control; low-load task) as the between-subjects factor and time (pre- vs posttraining vs 1- vs 3-month follow-up) as the within-subjects factor. Separate tests will be conducted with the emotional symptom scores, cognitive measures (ie, accuracy and RT), and math achievement scores as dependent variables. Intention-to-treat analyses will be used to account for missing data, as appropriate. Descriptive and inferential statistics will be performed using SPSS (IBM Corp). We will apply Bonferroni corrections to follow-up tests to control for type 1 error.

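### Holm's step-down in place of single-step Bonferroni for the follow-up tests would be a cheap, optional power gain; Bonferroni is valid, and the gain depends on a family the article does not state

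*Protocol article*

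**What the plan says.** The Data Analytic Plan runs a separate 2 x 4 mixed ANOVA for each outcome, with group as the between-subjects factor and "time (pre- vs posttraining vs 1- vs 3-month follow-up) as the within-subjects factor". On multiplicity it says only: "We will apply Bonferroni corrections to follow-up tests to control for type 1 error". It names no step-down version and does not say which comparisons form the family. It also gives no numeric alpha.

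The Results paragraph of the Abstract predicts gains from pre- to posttraining and that "these effects will be maintained at 1- and 3-month follow-ups, compared to children in the active control group". The Discussion repeats the prediction. If it is right, several follow-up contrasts within one outcome are non-null together.

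The Participants section states that "66 participants are required to detect small effects" (d=0.20) "with 80% or greater power on primary outcome measures relative to controls", and "To allow for approximately 30% attrition we will recruit 100 children".

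**The concern.** Bonferroni tests every one of m comparisons at 0.05/m. Holm orders the p values and tests the smallest at 0.05/m, the next at 0.05/(m-1), and so on, stopping at the first failure. Both hold the familywise error at or below 5% whatever the dependence among tests. Holm's thresholds are never stricter, so it rejects all that Bonferroni rejects and sometimes more.

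The difference is largest when many contrasts in the family are truly non-null, and a maintained effect is that situation for the baseline-to-visit contrasts. With a constant true effect and modest numbers, Bonferroni more often gives significance at some visits and not at others. Readers may take such a pattern for fade-out.

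**Working it through.** **Inputs from the article.** Four time points; Bonferroni for follow-up tests; a prediction that the effect is maintained; planning effect d=0.20; 66 children required, 100 recruited, about 30% attrition.

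**Assumptions, because the article does not give them.** Two-sided 5% familywise alpha; 1:1 allocation (the article says only "We will randomly assign participants to 1 of the 2 training groups"); equal correlation r between all visits, with 0.7 as the reference; the same group difference d, in units of the single-visit SD, at all three later visits.

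**The plan's own figures.** Attrition: 66/0.7 = 94.3, so 95 are needed and 100 suffices. Also 100 x 0.7 = 70 completers, or 35 per arm. The figure of 66 for d=0.20 cannot be confirmed or refuted from the stated inputs: a 2 x 4 interaction with f=0.10 returns 66 only at an unstated correlation of about 0.765 to 0.77. It does not bear on the choice between Bonferroni and Holm.

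**Bonferroni, one contrast, by formula.** SD of change = sqrt(2(1-r)) = sqrt(0.6) = 0.775. Noncentrality = (d/0.775) x sqrt(35/2). For d=0.4 this is 0.516 x 4.183 = 2.16, on 68 df.
- Three contrasts: threshold 0.05/3 = 0.0167, critical t = 2.455, power 39%.
- Six pairs: threshold 0.05/6 = 0.0083, critical t = 2.718, power 30%.

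**Bonferroni against Holm, simulated.** Child-level data, 35 per arm, two-sided t tests on change, 20,000 to 60,000 replicates. Power per contrast and the chance that all are significant refer to the three baseline-to-visit contrasts.

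| Family | r | d | Power per contrast | All three significant |
|---|---|---|---|---|
| 3 contrasts | 0.7 | 0.4 | 39% v 45-46% | 16% v 29% |
| 3 contrasts | 0.7 | 0.5 | 60% v 68% | 35% v 53% |
| 3 contrasts | 0.5 | 0.4 | 22% v 26% | 6% v 13% |
| 3 contrasts | 0.8 | 0.4 | 58% v 66% | 32% v 50% |
| 6 pairs | 0.7 | 0.4 | 29.5% v 31.4% | 10% v 13% |
| 6 pairs | 0.7 | 0.5 | 50% v 53% | 25% v 30% |
| 3 contrasts | 0.7 | 0.2 | 9% v 11% | 1.3% v 3.6% |
| 3 contrasts | 0.5 | 0.2 | 6% v 7% | 0.6% v 1.9% |
| 6 pairs | 0.7 | 0.2 | 6% v 6% | 0.5% v 0.9% |

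The gain is small with six pairs because, when the effect is maintained, the three comparisons among later visits are true nulls. Holm then rarely steps down far.

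**What does not change.** The first Holm step is the Bonferroni threshold, so the chance of at least one significant result in the family is identical: 64% for both with three contrasts, r=0.7 and d=0.4. If only posttraining differs (33 per arm, d=0.5), power for that contrast rises by 0.1 point.

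**Type 1 error.** With no true effect, the familywise error is the same for both methods (about 4.6% at r=0.7). With one true effect it rises from about 3.2% to about 4.0% under Holm, still within 5%.

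**Mixed patterns.** With three contrasts, r=0.7 and d=0.4, the chance that some but not all are significant falls from about 48% to 35% (64% minus 16%, and 64% minus 29%).

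**The case against.** The strongest reply is that nothing is wrong with the plan. Bonferroni is valid, conventional and conservative, and it does what the article asks of it, namely "to control for type 1 error". Preferring Holm is advice that would fit almost any protocol that uses Bonferroni. This stands: the point concerns efficiency and is neither an error nor a contradiction.

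The reply also has force on size:
- A reader might infer that the plan forfeits nearly half of its chance of confirming maintenance (16% against 29%). The article does not support that. The figure needs a three-contrast family that is nowhere stated. The Study Design section can be read as including posttraining against follow-up comparisons, and under six pairs the gain is about 3 points.
- The figure also uses d=0.4, twice the planning value. At d=0.20 the chance of all three is below 5% under either method in the settings tabulated.
- No section makes significance at all three visits a success criterion. The Abstract and Discussion predict maintenance but set no such rule. Reading a mixed pattern as fade-out would in any case be a misreading of a nonsignificant result, and Holm still leaves that pattern at about 35%.
- Holm dominates in rejections only. Bonferroni comes with matching simultaneous intervals and Holm does not.

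What survives is that, for the decisions themselves, Holm can only gain, under the same error bound, whichever family is intended.

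**Conclusion.** The point holds as an optional improvement. Single-step Bonferroni is valid but never more powerful than Holm at the same 5% familywise bound. That direction is a mathematical property and needs none of the assumptions above.

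The size does need them. At d=0.4 and correlation 0.7, the gain per contrast is about 6 to 7 points with three contrasts and about 2 points with six pairs. For all three baseline contrasts together it is about 13 and 3 points. At the trial's own d=0.20, with three contrasts and correlation 0.5 to 0.7, the chance of all three rises by about 1 to 2.5 points. Holm helps a claim of persistence across visits and does nothing for first detection. A reader should not infer that the analysis is invalid or that the predicted maintenance cannot be tested under Bonferroni; the article supports neither.

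**What to change.** In the last sentence of the Data Analytic Plan, replace 'Bonferroni corrections' with 'Holm-Bonferroni (step-down) corrections' for the follow-up tests within each outcome, and name the family the investigators intend. If that family is the group difference in change from pretraining at posttraining, 1 month and 3 months, the smallest p is compared with 0.05/3, the next with 0.05/2 and the largest with 0.05, stopping at the first failure.

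The cost is one sentence. The p values from SPSS can be ordered and compared by hand, and no extra children or data are needed. The Results section says that analysis starts after data collection ends, so the wording can be settled before results are analysed.

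The downside is in the intervals. Report Bonferroni-adjusted intervals, or unadjusted 95% intervals labelled as such, beside the Holm decisions. State that they need not agree with those decisions: an adjusted interval may include zero where Holm rejects, and an unadjusted one may exclude zero where Holm does not. If the investigators value matching simultaneous intervals more than the extra power, keeping Bonferroni is defensible.

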## Results

Recruitment and testing opened in September 2023 and will continue for 12 months. We will begin analyzing our data on the completion of the data collection, and the publication of results is expected by the end of 2024.

## Discussion

This study will examine the effect of inhibitory control training on anxiety and math achievement in children aged 8-10 years, relative to an active control condition. We predict children in the CCT group will report reduced emotional symptoms (anxiety, worry, depression, and rumination) and demonstrate improved inhibitory control, shifting, updating, and math achievement when comparing pre- to posttraining, 1-, and 3-month follow-up, relative to controls. Results will inform whether inhibitory control training affords promise as an intervention for anxiety in this age group and advance knowledge of factors affecting math achievement. These findings would provide a foundation for the development of a training app that has the capacity to reach those not well-served, be delivered on large scale for low cost, and afford the possibility of administration across a wide range of settings [4].

This research has several limitations worth noting. We realize using a small sample of children aged 8-10 years means we may not be able to generalize our findings to a larger population or a broader age group. However, pending our results, we aim to replicate our work using a larger cohort and a randomized control design. There are constructs outside the scope of this project. For example, our design will be unable to determine whether inhibitory control training affects other educational outcomes, especially language and reading, which are linked to math achievement. With these potential shortcomings in mind, we hope this work becomes the catalyst for other research using CCT paradigms with children.

## Appendix

Multimedia Appendix 1 Peer reviews.

## Abbreviations

ADHD: attention-deficit/hyperactivity disorder
aGo/No-Go: adaptive Go/No-Go
CCT: cognitive control training
RT: reaction time
